## Abstract

**Background:**

Swedish child healthcare involves school health services, primary healthcare, and pediatric clinics. Family-based programs addressing child diet, eating behavior, parental feeding practices and physical activity show promise for preventing and treating overweight in children 2–12 years, but organizational gaps hinder coherent implementation of interventions. The novel Co-Fam model integrates two complementary programs: the universal Healthy School Start (HSS) family support program, delivered in schools during grade 1, and the targeted 12 months More and Less (ML) parental support program, provided through primary healthcare to treat children 6–12 years with overweight and obesity. ML consists of ten group sessions with parents, followed by individual booster sessions. The dual primary aim of this study is to evaluate the effectiveness of the ML program on child bodyweight development and to assess implementation outcomes fidelity, acceptability, feasibility and cost-effectiveness of the Co-Fam model.

**Methods:**

The setting for this study is a municipality in Region Stockholm with high cultural diversity and health needs, which has been running the HSS program since 2022. In this hybrid type 2 effectiveness-implementation study with two parallel arms, children aged 6–12 years with overweight or obesity will be randomized to either the ML program or standard care. Primary effectiveness outcomes are BMI z-score and %IOTF-25 measured at baseline, three and 12 months. Secondary outcomes are waist-to-height-ratio, parental feeding practices, child physical activity, diet and eating behavior. Primary implementation outcomes are fidelity to the ML program assessed at three and 12 months. Acceptability and feasibility of the Co-Fam model will be assessed three to 12 months after start, through semi-structured interviews with parents and providers. A health economic evaluation will be conducted using a cost-utility design.

**Discussion:**

We hypothesize that ML will be more effective than standard care in reducing overweight and obesity in children. The integration of the HSS and ML programs in the Co-Fam model is expected to enhance collaboration between school and healthcare and ensure early identification of at-risk families. The dual focus on effectiveness and implementation will inform the scalability and sustainability of the Co-Fam model with implications for policy and practice in child obesity prevention and management.

**Trial registration:**

The trial was registered at Clinicaltrials.gov, September 11-2025, ID: NCT07158944.

**Supplementary Information:**

The online version contains supplementary material available at https://doi.org/10.1186/s12889-026-29530-3.

## Background

Reducing overweight and obesity in children is a global public health priority [1]. In Sweden, about one in five children aged 6–9 years have overweight (15%) or obesity (6%) [2]. The prevalence is rising across all population groups, with a pronounced social gradient, disproportionately affecting individuals with lower educational attainment, low income, single parent households [3], and individuals born outside of Europe [4]. The development of obesity is complex, influenced by genetic predisposition, environmental and social conditions as well as health related behaviors such as physical activity and dietary habits [5]. Children living with obesity face an increased risk of cardiovascular morbidity [5] and type 2 diabetes (T2D) in adulthood [6, 7]. In addition, individuals with overweight or obesity often experience weight-related stigma, which can lead to psychological distress, including low self-esteem, depressive symptoms, and anxiety, and may contribute to unhealthy coping strategies and avoidance of healthcare [8]. Fortunately, evidence based person-centered pediatric obesity treatment can help reduce these risks, improving long-term health outcomes by lowering the likelihood of T2D, dyslipidemia, and hypertension, and even decreasing mortality rates in young adulthood [9].

Overweight and obesity impose substantial lifetime societal costs, primarily due to elevated healthcare expenditures and productivity losses [10]. More specifically, the average incremental lifetime healthcare cost for a 6-year-old child with obesity in Sweden, compared to a child with normal weight, is estimated at approximately €39 270 for girls and €23 741 for boys [10]. For children with overweight, the corresponding cost is around €13,700 for both sexes [10]. Furthermore, children with a high body mass index (BMI) experience increased lifetime productivity losses later in life due to temporary and permanent sick leave, as well as increased risk of unemployment [10]. Around 50% of children who have developed obesity before puberty will continue to live with obesity during adolescence, and of these, around 80% will have obesity in adulthood [11]. Hence, the complexity related to obesity development calls for a dual approach of prevention and management including *universal* components for all children such as promoting healthy eating habits and physical activity in healthy school and home environments [12] as well as *targeted* interventions for high-risk children focusing on behavior change [13].

Family-based interventions involving parents only, alternatively parents and children, are recommended for obesity prevention for children up to 12 years of age, since parents influence and to a large extent have control over their child’s environment [14–17]. Family-based interventions can improve child weight and/or weight-related behaviors [17, 18]. Interventions often focus on diet and physical activity, sometimes including screen time and sleep. They are usually provided by primary healthcare (PHC), schools, or other actors in the community [15, 16]. Effective interventions focus on parenting skills and practices, role modelling and strategies for managing children’s behavior, such as reinforcement [17], grounded in social learning theory [19]. Systematic reviews further recommend multi-component behavior change interventions to prevent and manage childhood obesity [18, 20, 21]. While school-based interventions show effectiveness regarding prevention [22], family-based interventions are effective in reducing the BMI of children with obesity [18, 20]. However, the effectiveness of interventions depends not only on parental involvement but also on broader contextual factors, including family functioning, cultural and socioeconomic circumstances, and access to resources [18]. The largest reductions in BMI z-score have been observed in younger children, particularly those aged 2–5 years, followed by children aged 6–11 years when participating in comprehensive, multicomponent interventions for overweight and obesity [21]. It is generally recommended that family-based interventions should last at least six months [23].

In Sweden, national guidelines for the treatment of children with obesity recommend family support and combined health behavior treatment, including at least 26 contact hours with a multidisciplinary team with child competence [24–26]. The type of treatment, number of visits and overall intensity should be tailored by the clinician to individual needs, age, degree of obesity and any comorbidities. While some regions in Sweden offer either individual or group-based parental support, these approaches have not been systematically evaluated for children aged 6–12 years.

Based on the Exploration, Preparation, Implementation, Sustainment (EPIS) framework [27], we developed the Co-Fam model together with school health services, PHC including dieticians and physiotherapists, a pediatric clinic (PC) and parents to increase acceptability and feasibility [28, 29]. Obesity treatment for children in Sweden involves a collaboration between schools run by municipalities or private corporations, and healthcare run by regional authorities [30], all publicly funded. Implementation of interventions in multi-organizational settings needs careful planning to be successful. The Co-Fam model combines the universal “Healthy School Start” (HSS) family support program delivered by school personnel in grade one with a focus on health promotion and prevention with the targeted “More and Less” (ML) obesity treatment program offering parental group sessions by PHC personnel. The HSS program has been evaluated for children aged 5–7 in three cluster-randomized controlled trials with beneficial effects on diet [31–33], and a significant decrease in BMI in children with obesity [12]. The more intense and targeted ML program for parents of children aged 2 to 6 years with overweight or obesity has shown clinical effectiveness in two randomized controlled trials [13, 34, 35]. In order to maintain and enhance the weight change seen in the HSS program for children with higher needs, the ML program could be effective. Accordingly, the Co-Fam model builds on a combination of the HSS and ML program. This requires adaptation of ML for parents of children aged 6 to 12, for whom evidence-based parental support is not available in Sweden. The Co-Fam model is novel in the since that it integrates these two programs across settings and levels of care, creating a coherent pathway from universal prevention to targeted treatment according to child needs.

We hypothesize that combining the HSS and ML programs in a coherent model will be feasible and acceptable, increase health literacy, ensure early identification of families in need, and enable early treatment of overweight and obesity. In addition, we hypothesize that it will lead to better collaboration between school health services, primary and specialized healthcare, ultimately improving prevention and treatment of children with overweight and obesity. This study aims to evaluate both the effectiveness of the ML program and implementation of the Co-Fam model in the Swedish context.

The specific research questions are:

What is the effectiveness of the 12-month ML program on children’s weight development, compared to standard care for overweight and obesity in 6 to12 year-old children?What are the effects of the ML program on children’s diet, eating behavior, physical activity and on parental feeding practices, compared to standard care?Is the Co-Fam model acceptable, feasible, and cost-effective?

## Methods

### Co-design and public involvement

Phase 1 of the Co-Fam project, the exploration and preparation phase of the EPIS framework [27], involved a co-design process in which personnel from school health services, PHC, PC, and parents participated in workshops. The workshops aimed to identify barriers and facilitators, and to develop and tailor the implementation strategies to the context to establish high acceptability. This protocol paper describes phase 2 of the Co-Fam project, the implementation phase.

### Study design

In this hybrid type 2 effectiveness-implementation study [36] with two parallel arms, children aged 6–12 years with overweight or obesity will be randomized to either the ML program or standard care. The universal HSS program has been running in primary schools in the municipality since 2022. The intervention arm will receive the ML program adapted to children 6–12 years by the researchers who developed the program who are part of the research team (PN and AE). The control arm will receive standard care for overweight or obesity. Both arms are followed over a period of 12 months. Personnel from school health services, PHC, and PC will be involved in recruitment, implementation and follow-up. PHC personnel, mainly dieticians and physiotherapists, have been trained as group leaders and will deliver the ML program to parents.

The study will be conducted in line with the ethical principles for medical research involving human subjects in the Declaration of Helsinki [37]. This protocol was developed in accordance with the

Standard Protocol Items: Recommendations for Intervention Trials (SPIRIT) guidelines [38]. The intervention is reported using the template for intervention description and replication (TIDieR) [39] checklist. The guidelines are presented in Supplementary Table 1.

### Study setting

The study will take place in a municipality with 19 public primary schools with a prevalence of childhood obesity among the highest in the Stockholm region [40]. Based on routine data it is estimated that approximately 1,800 children aged 6–12 years in this municipality are living with overweight or obesity, some of whom receive care in the primary or specialist setting. The municipality has just over 100,000 inhabitants out of which more than 44% are born outside of Sweden, twice as many as the national average [41].

In Sweden, access to school health services is mandatory and regulated by law [42]. National guidelines mandate that school health services offer health checks for children on at least three occasions during grade one to six (age 6–12 years) including at least two measurements of height and weight [42]. Children classified as having overweight according to International Obesity Task Force (IOTF) criteria [43] are entitled to support from PHC while children classified as having obesity are entitled to treatment from specialized pediatric care [25]. If a school nurse identifies a child with obesity, a referral is sent to a pediatric clinic (PC) after informing the parents. In case of overweight, a referral is usually sent to PHC in agreement with the child’s parents for a meeting with a dietitian or physiotherapist [25]. Table 1 includes a detailed description of the guidelines. School health services, PHC and PCs can be under public or private governance, but all are publicly funded. This creates challenges for communication and coordination between different levels of care, as the use of separate medical record systems means that school health services often lack easy access to information about a child’s treatment in primary and specialist care [30]. The Co-Fam model has been designed to bridge this gap and to ensure coherent support according to needs.

**Table 1 Tab1:** National and regional recommendations for management of overweight and obesity for children up to 12 years

	Overweight	Obesity
Provider	School and Primary healthcare	Specialized pediatric clinic in collaboration with primary healthcare
Diagnosis	Growth curve (BMI z-score) and assessment of health behaviors in the family	Growth curve (BMI z-score), assessment of health behaviors in the family, blood samples of the child to check for co-morbidities
Recommended treatment	Provide basic advice on nutrition and physical activity Offer individual or family-based support for children with unhealthy eating habits and/or insufficient physical activity, including: -Counseling -Motivating strategies -Behavior change strategies -Positive reinforcement -Parental support Identification of children at risk of developing obesity, refer children who develop obesity to a pediatric clinic	Combined health behavior treatment -Individual and parental support with healthy eating habits, physical activity and sedentary behavior -Support for behavior change regarding sleep, stress and self-regulation -Long-term support to maintain behavior change At least 6 visits per year including a yearly check-up with a pediatrician and contact with a dietician and physiotherapist A recommendation of at least 26 h of treatment per year Parental support programs and digital support are offered depending on availability and interest In case of severe obesity with complications, families can be referred to the National Centre for Child Obesity. Medications can be prescribed as a complement to combined health behavior treatment (if child is > 12 years)
References	[14]	[25, 44]

### The Co-Fam model

The Co-Fam model (Fig. 1) illustrates a coherent model of family support, combining the universal HSS and the targeted ML program. Together, the two programs aim to promote healthy habits and positive parenting practices to prevent and treat overweight and obesity in children. The model builds on a close collaboration between families, school health services, PHC and PC, recognizing the importance of each actor in supporting the child´s development and maintaining a holistic perspective with the family in the center. The arrows represent referrals of children diagnosed with overweight or obesity between school health services, PHC and PC. The arrow between PHC and PC indicates collaboration in offering treatment options for families with higher needs.

**Fig. 1 Fig1:**
[figure not shown]
The Co-Fam model

The HSS program has been provided in grade one to all children and their families attending public schools in this municipality since 2022. The program is based on Social Cognitive Theory [19] and consists of four components: (1) A parental guide with health information available in 11 languages; (2) a motivational interview with parents performed by the school nurse; (3) classroom activities for the children performed by teachers with home assignments; and (4) a T2D risk self-assessment test for parents [44]. For a detailed description of the HSS program see Elinder et al. [45]. The HSS program has been evaluated regarding implementation showing that the program can be performed with relatively high fidelity, although somewhat lower in families with a non-Nordic background mainly due to language issues when performing the motivational interview [46]. Qualitative studies with school personnel and families have shown that teachers, school nurses, parents and children overall have a positive attitude towards the program and that it has raised the health literacy of the participants in both theory and practice [47–50].

The ML parental support program is grounded in Social Learning Theory [51, 52] and Social Interaction Learning Theory [19, 51] which together emphasize how parenting practices, social interactions, and broader environmental contexts influence children’s behaviors [53]. The ML program is based on a manual and consists of ten weekly 90-minute group sessions, led by primary healthcare personnel (HCP) (dieticians and physiotherapists) trained as group leaders (Table 2). The group sessions are followed by six individual booster sessions every six weeks for another nine months. Group sessions focus on strengthening parent-child communication to achieve healthy behaviors through evidence-based parenting practices, including positive reinforcement and role modeling, with role play and peer discussions as key components for building skills. Parents receive handouts briefly outlining the content of each session, including home assignments. The booster sessions focus on the families’ individual needs and provide an opportunity to follow up on the relevant topics covered during the group sessions.

**Table 2 Tab2:** Content of the group sessions in the More and Less parental support program (month 1–3)

Session	Topic	Content overview
1	Introduction and parents’ key roles	Presentations, aim of program, parents’ key roles and why treatment of obesity.
2	When More and when Less?	Tools for healthy eating, screen-time, physical activity, and sleep.
3	Cooperation and encouragement	Importance of cooperation and encouragement in the family. What is an appropriate portion size.
4	Teaching new behaviors	Encouragement and incentives. Setting up house rules. Being aware of the influence of social media.
5	Using charts and incentive systems	Using incentive systems to learn new behaviors. Promoting body satisfaction and positive self-esteem in the child.
6	Parents as teachers: To prepare and to plan	How to decrease conflicts. Healthy food choices – the Keyhole symbol and snack meals.
7	Setting limits	To set limits - why and how? The plate model.
8	Power-struggles	Avoiding and disengaging from power struggles. Keeping emotions under control. Improving recipes.
9	More support Less stress	How to handle stress and involve their network. Promote mental health.
10	Summary and preparation for the future	Lessons learned and moving forward. Promote social contacts.

### Intervention arm: the ML program

Families in the intervention arm will receive the 12-month ML group-based program. Over the study period (January 2026 – December 2028), two ML groups will be initiated every six months, each including 6–10 parents. Group sessions will be offered weekly, either face-to-face at PHC clinics or online, while booster sessions will be provided by phone or videocall. If a parent misses a session, a follow-up call is offered. If a parent does not attend any of the first three sessions, they will be invited to join the next available group in the study.

### Control arm: standard care for overweight or obesity

Standard care for overweight [54] and obesity [25] is based on national guidelines (Table 1) where children with obesity are referred to a pediatrician for yearly check-ups often in combination with follow-up visits to a pediatric nurse, dietician and/or physiotherapist. For some children, referral to a psychologist can also be part of obesity treatment. They also have the option to receive a digital support tool. For children with overweight, parents are offered referral to the PHC for support by a dietitian and physiotherapist. All children’s weight, height, and waist circumference will be measured on three occasions (Fig. 2). A timeline of the study procedures is illustrated in Fig. 2.

**Fig. 2 Fig2:**
[figure not shown]
Study timeline. Abbreviations: pt; participant

### Register-based control group

In addition to the randomized controls, data from the Swedish National Child Obesity Treatment Register BORIS, started in 2005 [55], will be collected retrospectively to enable a national comparison of the effect of standard treatment to the ML program for children with obesity. Data from children in the BORIS registry will be selected randomly in a 1:3 ratio matched to children with obesity in the intervention arm on age (± 100 days), sex, BMI z-score at baseline and year of treatment initiation. The type of care received will be documented retrospectively over a period of 12 months based on registry data.

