### Inclusion and exclusion criteria for the trial

Eligible participants are parents of children between 6 and 12 years of age who have children with overweight or obesity according to IOTF criteria [43]. Children taking medication affecting weight development will be excluded from the study. Families in the intervention group are advised not to participate in other forms of structured treatment during the study period. The ML group sessions will be conducted in easy Swedish and potentially in other languages depending on needs.

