### Data collection

Data collection activities, time points, and data sources are shown in Table 4. Children’s height, weight, and waist circumference will be measured by the school nurse at three timepoints. Parents will answer a baseline questionnaire including demographic data (sex, age, country of birth, years in Sweden, education, housing situation, employment status, weight, height, number of children) and their child (sex, age, country of birth, school, treatment clinic, additional diagnoses). Questionnaires regarding the child’s diet and physical activity habits, the child’s eating behavior, and parental feeding practices are included in the three assessments. Questionnaires can be answered from a mobile phone/tablet/computer, at a convenient time for the participant. Data regarding number of treatment visits and comorbidities will be collected from the child’s medical journal. Data on implementation outcomes will be collected from parents and HCPs via questionnaires distributed during the study period and semi-structured interviews performed after participation in the ML program. Data from the BORIS registry [55] will be collected retrospectively.

**Table 4 Tab4:** Data collection and time points

TIMEPOINT	Enrollment and randomization	TRIAL PERIOD		
	Pre-intervention	T0	T1	T2
ENROLLMENT:	X			
Eligibility screen	X			
Informed consent	X			
Randomization	X			
INTERVENTION/COMPARATOR:				
* Intervention: More and Less*		X	X	X
* Comparator: Standard care*		X	X	X
* Comparator: Register control*		X	X	X
ASSESSMENTS: Effectiveness outcomes				
* Child’s eating habits*		X	X	X
* Child’s physical activity*		X	X	X
* Child’s eating behavior*		X	X	X
* Parental feeding practices*		X	X	X
* Child’s weight*,* height and waist*		X	X	X
ASSESSMENTS				
* Demographics*		X		
* Adverse events*			X*	X*
* Fidelity*			X	X
* Feasibility*				X
* Acceptability*				X
* Cost*				X

*Data on adverse events is collected continuously. Abbreviations: T0, baseline; T1, 3-month follow-up, T2, 12-month follow-up

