### Data analysis

All analyses will be performed as an intention-to-treat analysis. Descriptive statistics will be used to summarize participant characteristics at baseline per study arm. Prior to analysis, the distribution of the outcomes will be assessed for normality and homogeneity. Between arm differences for outcomes, BMI z-score (primary outcome), %IOTF-25, probability of reaching BMI z-score cut-offs and WHtR will be analyzed.

To analyse the primary outcome of BMI z-score we will fit a linear mixed model with BMI z-score at 0, 3, and 12 months as the outcome variable, including a random intercept for each child. Fixed covariates will be treatment assignment (ML or control), time (in months), their interaction, and baseline weight status. The effect of the treatment will be assessed by the interaction parameter, which is interpreted as the difference in change of BMI z-score per month” between the two randomisation arms. A dose-effect analysis will be performed to assess the effect of number of ML sessions attended. This will be performed by replacing the treatment variable in the regression model with a variable indicating how many sessions the child’s parents attended.

The register control arm will be compared against the ML arm regarding BMI z-score, %IOTF-25, probability of reaching BMI z-score cut-offs and WHtR, using the same methods as described above adjusted for confounders. Secondary outcomes will be analyzed using the same principles as above. Interviews with parents and HCP will be transcribed verbatim and analyzed using reflexive thematic analysis [73–75]. We will explore causal pathways between effectiveness- and implementation outcomes by integrating the quantitative and qualitative data. Missing data will be evaluated for its extent and patterns. If missingness in key outcomes (e.g., BMI z-score, %IOTF-25, BMI z-score cut-offs, WHtR) exceeds a predefined threshold, appropriate statistical methods such as multiple imputation will be applied. Full details about the analysis will be described in the Statistical Analysis Plan, which will be finalized and published in Clinicaltrials.gov before the end of data collection.

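### The register comparison mixes the ML effect with everything else that separates trial children from register children, and the plan omits the benchmark its randomised controls could supply

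*Protocol article*

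**What the plan says.** The section on the register-based control group adds register children to the randomised controls. They are "selected randomly in a 1:3 ratio matched to children with obesity in the intervention arm", with matching "on age (± 100 days), sex, BMI z-score at baseline and year of treatment initiation". The purpose given is "to enable a national comparison of the effect of standard treatment to the ML program for children with obesity". The Data analysis section fixes the contrast: "The register control arm will be compared against the ML arm regarding BMI z-score" and three other outcomes, by the methods used for the randomised arms and with adjustment for confounders. No comparison of the register children with the randomised controls is described.

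Other sections describe the setting of the trial children:

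- **School programme.** "The HSS program has been provided in grade one to all children and their families attending public schools in this municipality since 2022" (section on the Co-Fam model). The Discussion adds that families cannot opt out. The Background credits HSS with "a significant decrease in BMI in children with obesity".
- **Participation.** Families are consenting volunteers who receive a voucher at the end (Recruitment section).
- **Measurement.** Height, weight and "waist circumference will be measured by the school nurse at three timepoints" (Data collection). Register values are collected retrospectively.
- **Place.** More than 44% of the municipality's inhabitants were born outside Sweden, twice the national average (Study setting).

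**The concern.** The register comparison asks how ML performs against standard treatment nationally. An ML child and a matched register child differ in ML, but also in having volunteered for a trial, in being measured at fixed times by a school nurse, largely in municipality, and to a large extent in HSS exposure. The first two coincide exactly with the grouping variable and the others nearly so. A regression has little or no overlap from which to estimate them separately, whichever confounders are finally chosen.

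A difference from the register could therefore appear without any ML effect, or a real ML effect could be masked. The trial already holds a group that can indicate how large the background difference is: the randomised controls with obesity. They come from the same municipality, recruitment process and measurement route. As written, the plan does not set them against the register.

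**Working it through.** **Reproducing the plan's own figure.** Inputs from the Sample size section: difference 0.16, SD 0.3, power 80%, alpha 0.05 (taken as two-sided), 10% loss.

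- Per arm: 2 × (0.3 × (1.960 + 0.842) / 0.16)² = 55.2, rounded up to 56.
- After loss: 56 / 0.9 = 62.2, rounded up to 63; total 126, as stated.

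No sample size is stated for the register comparison.

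**Children with obesity per arm.** The documents do not give the share of the sample with obesity. The lower assumption is the national ratio in the Background, 6% / (15% + 6%) = 29%. The upper value of 65% is an assumption without a source in the documents. With 63 × 0.9 = 56.7 children followed per arm:

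- 29%: n = 16; 50%: n = 28; 65%: n = 37.

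**Precision.** Independent children, SD 0.3, three register children per trial child, correlation from matching ignored.

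| n | SE against register, 0.3 × √(1/n + 1/(3n)) | 95% half-width | SE against randomised controls with obesity, 0.3 × √(2/n) |
|---|---|---|---|
| 16 | 0.087 | 0.17 | 0.106 |
| 28 | 0.066 | 0.13 | 0.080 |
| 37 | 0.057 | 0.11 | 0.070 |

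The planned randomised comparison uses all children: 0.3 × √(2/56.7) = 0.056.

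**Effect of a background shift b with no ML effect.** Probability of two-sided rejection = 1 − Φ(1.96 − b/SE) + Φ(−1.96 − b/SE). The values of b are assumptions.

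| b (BMI z) | n = 16 | n = 28 | n = 37 |
|---|---|---|---|
| 0.03 | 6% | 7% | 8% |
| 0.05 | 9% | 12% | 14% |
| 0.10 | 21% | 33% | 42% |

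**What the benchmark can show.** Controls with obesity versus the register set has the same SE as ML versus register, because the group sizes are the same. Its 95% half-width is thus 0.11 to 0.17 against a target effect of 0.16, and its power to detect a true shift b is the value in the last table. It would often miss a shift of 0.05 or 0.10.

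With a common register set, (ML − register) − (control − register) = ML − control. The benchmark therefore adds no information on the effect of ML. It shows how far trial children on standard care differ from register children.

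**The case against.** The strongest reply is that this comparison is supplementary. The register section presents it as additional to the randomised controls, and Data analysis places the treatment effect in the contrast between the randomised arms. That stands. A reader might infer that the register result could decide effectiveness, or would look more precise than the trial's main result. The documents support neither. The register SE is smaller only than that of the randomised subgroup with obesity, which Data analysis does not list. Against the full randomised comparison (0.056) it is no smaller (0.057 to 0.087).

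Second, HSS is easily overstated as a source of bias. Any HSS effect already present at enrolment is in the baseline BMI z-score, which is matched, so only a continuing or concurrent effect on later change matters. Exposure is also incomplete: it is limited to public schools and to grade one since 2022, so private-school pupils and the oldest early enrolees may lack it. This narrows the HSS argument but leaves volunteering and measurement route untouched.

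Third, one might infer that the randomised controls differ from the ML children only in ML. The Discussion acknowledges spillover, since ML group leaders care for both arms, and only intervention families are advised against other structured treatment. A difference between controls and register may therefore contain some ML effect. A rule that credits ML only with what the controls do not show would be too strict.

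Fourth, a reader might add that "Children taking medication affecting weight development will be excluded from the study" is not repeated for register children. That rests on silence, and Table 1 mentions medication only above age 12. Such filters and the list of confounders can properly be left to the statistical analysis plan.

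**Conclusion.** The point holds in a limited form. Trial participation and measurement route coincide with data source, and municipality and HSS exposure largely do. The planned adjustment cannot separate them from ML, so ML versus register does not isolate the effect of ML. Bias requires differences that act on change after baseline.

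The documents fix neither its size nor its direction. The rejection rates of 9% to 14% (shift 0.05) and 21% to 42% (shift 0.10) show what such shifts would do if present. They rest on the assumed shifts, an assumed obesity share of 29% to 65%, the plan's SD of 0.3 and a normal approximation with independent children. They do not estimate the actual bias.

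The randomised primary analysis and the sample size are unaffected. What changes is how much the register comparison can be said to show.

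**What to change.** In Data analysis, add the same register model for the randomised control children with obesity versus the register set. Either match register children to both arms, or use the set matched to the ML children; stratified randomisation by weight status makes that set a reasonable fit for the controls as a group. Report the result beside ML versus register as a benchmark for background differences, and state that ML versus register is a descriptive, non-randomised comparison.

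The cost is one extra model, with no extra participants or visits; matching both arms would also need a larger register extract. The benchmark cannot prove comparability, and it should not be subtracted as a correction: it is imprecise and may contain spillover. It sets a limit on what is claimed from the register.
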